### Stepped wedge trial design

We will use a stepped wedge controlled trial design [33], such that all sites will start with the less intensive implementation strategies (toolkit + IAU) before receiving the more intensive implementation support (toolkit + implementation facilitation) in a staggered fashion (Fig. 1). Stepped wedge designs have their roots in balanced incomplete block designs [34]. A stepped wedge has the advantage of minimizing burden on implementation support personnel as start times are staggered, with all sites ultimately receiving the implementation facilitation strategy. We aim to recruit 16–20 VA Medical Centers (VAMCs) as sites, with about six sites assigned to each of the three waves with start times staggered by 6-month intervals. All sites will start with 3 months in the less-intensive toolkit + IAU condition to allow the collection of baseline data. When each site switches to the more intensive intervention, they will receive 6 months of active implementation facilitation followed by 6 months of step-down.

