### Quantitative evaluation of the implementation outcomes

We propose to use RE-AIM as an evaluation framework to guide our qualitative analyses [30]. RE-AIM examines 5 dimensions: reach into the target population, effectiveness of the intervention, adoption by the setting, implementation fidelity, and maintenance (i.e., degree of sustainment over time). Of these, one (effectiveness of the intervention) pertains to clinical effectiveness (aim 2), while the remaining four relate to implementation (aims 1 and 3). Thus, RE-AIM is ideal for structuring the proposed hybrid implementation-effectiveness evaluation. Table 2 describes the specific outcome measures and data sources for each RE-AIM dimension. Given our hybrid type 2 design, we are equally interested in implementation and clinical effectiveness outcomes. For this program evaluation, our primary implementation outcome will be reach (i.e., the proportion of WVs eligible for IPV screening who receive the screening). Our primary clinical effectiveness outcome will be disclosure rates and post-screening psychosocial care use (i.e., the proportion of women with a positive IPV screen who accept a referral and use psychosocial services in the ensuing 2 months).

**Table 2 Tab2:** RE-AIM guides evaluation of the impact and clinical effectiveness of IPV screening programs

RE-AIM dimension (study aim)	Outcome measures	Numerator	Denominator	Data sources
Reach (aim 1): The proportion of eligible WVs receiving IPV screening program.	Proportion of WVs seen in primary care clinics during the last 3 months of each study phase who receive IPV screening	WVs who receive IPV screening as indicated by documentation (templated note, clinical reminder)	WVs seen in primary care clinics who are eligible for IPV screening (WVs seen in clinic with no screen in prior year)	VA Corporate Data Warehouse (CDW): IPV screening status from health factors in templated notes and clinical reminders
Effectiveness (aim 2): The clinical effectiveness of IPV screening programs on disclosure and post-screening psychosocial service use.	a. Proportion of eligible WVs who screen positive for IPV	a. WVs who screen positive for IPV	a. WVs who were screened for IPV	CDW: IPV screening status, responses, and referral disposition (accept or decline referrals) from health factors in note templates and clinical reminders; psychosocial service visits based on clinic stop codes

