Maintenance (aims 1 and 3): The degree to which IPV screening programs are sustained over time.	Repeat Reach analysis in last 3 months of study. Note: Implementation strategies and contextual factors impacting maintenance will be assessed via survey and key informant interviews	Same as Reach analysis above, but with data collection occurring 9–12 months after IF ends	Same as Reach analysis above, but with data collection occurring 9–12 months after IF ends	CDW: For repeat of Reach analysis

We will extract relevant administrative and clinical data for all VAMCs from the VA Corporate Data Warehouse (CDW) for all five dimensions of RE-AIM (see Table 1 below for details). The templated note or clinical reminder is required for the study and includes health factors for IPV screening (i.e., disclosure), response (i.e., resources provided), and referrals offered (i.e., accepted or declined IPV Assistance Program-Coordinator referral; accepted or declined psychosocial services referral). Psychosocial care use, and time to first post-screening psychosocial care use, also come from CDW based on clinic stop codes for social work, psychology, psychiatry, primary care mental health integration, drug or alcohol treatment, and housing services.

Our operation partners are interested in testing whether a brief 1-item screener can be as effective as a more comprehensive (but lengthier) 5-item screener a modified Hurt, Insult, Threaten, Scream tool [40], which has been validated for use with the WV population [9, 32]. The tool asks individuals to indicate how often in the past year a current or past partner has done any of the following: “insulted or talked down to you,” “screamed or cursed at you,” “threatened you with harm,” “physically hurt you,” or “pressured or forced you to have sexual activities.” Response options for each item ranges from 1 (never) to 5 (frequently). Endorsement of any item indicates a positive screen. A more efficient screening tool could potentially enhance the uptake of IPV screening programs. However, prior to formal adoption of a 1-item tool, it is critical to evaluate the effectiveness of the tool in eliciting IPV disclosures (sub-aim 2a). The item was developed by a panel of IPV and women’s health clinical experts and researchers and consists of “In the past 12 months, have you experienced insulting, screaming, threatening, hitting, or unwanted sexual activity by a former or current partner?”

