We will use repeated measures generalized estimating equations (GEE) [41–43] analyses to address our study aims while controlling for site characteristics (between-site effects) and calendar time, which reflects secular trends (within-site effects). GEE quantifies and apportions the variance in outcomes among relevant factors, thus isolating the change in outcome due to the primary contrast of interest. It extends the traditional general linear model with a continuous outcome (e.g., linear regression) to accommodate binary outcomes for each subject and count outcomes for each site. GEE also accommodates repeated measures (within-subject correlation), random effects (subject), moderate imbalance among independent factors (sites), and various types of missing data. We will include relevant demographic and clinical variables at the patient level (e.g., age, mental health diagnoses, recent psychosocial service use) as covariates. Furthermore, GEE will allow us to explore the results for the patterns of unequal variance, relevant correlation structures, and variance component models to ensure that our results are robust. Our planned sample size will also support the exploration of many site-specific effects by adding site-interaction terms to the model. This method will also allow us to explore the study outcomes using a nested approach (WVs within VAMCs within study conditions). We will use the same GEE-based approach for encompassing each of the five RE-AIM outcome domains included in Table 2 above. Specifically, each primary outcome listed in Table 2 can be expressed as a proportion, and so columns for numerators and denominators are included. Analyses in each of these domains within the GEE framework will consist of logistic regression with random effects.

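### Table 2 times Maintenance both at the end of the study and 9–12 months after facilitation ends; with staggered waves, one calendar window can match at most one wave of three

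*Protocol article*

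**What the plan says.** All timings come from the protocol article.

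- **Table 2, Maintenance, outcome column:** "Repeat Reach analysis in last 3 months of study".
- **Table 2, Maintenance, numerator and denominator columns:** "Same as Reach analysis above, but with data collection occurring 9–12 months after IF ends".
- **Table 2, Reach, which Maintenance repeats:** "Proportion of WVs seen in primary care clinics during the last 3 months of each study phase who receive IPV screening".
- **Stepped wedge trial design:** 16–20 centres, "with about six sites assigned to each of the three waves with start times staggered by 6-month intervals". Also: "All sites will start with 3 months in the less-intensive toolkit + IAU condition to allow the collection of baseline data". After crossover, "they will receive 6 months of active implementation facilitation followed by 6 months of step-down".
- **Quantitative evaluation section, model:** GEE "controlling for site characteristics (between-site effects) and calendar time, which reflects secular trends (within-site effects"). For the scope of that model: "We will use the same GEE-based approach for encompassing each of the five RE-AIM outcome domains included in Table 2 above".

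The text gives neither the month in which the study ends nor the functional form of calendar time. Fig. 1, which shows approximate data-collection timing, is not available here.

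**The concern.** The outcome column reads as a calendar date common to all sites. The numerator and denominator give a date that moves with each site's own facilitation period. In a design with staggered starts these differ for most sites, so two analysts following the same table row could extract different months and report different sustainment results.

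The choice also affects what can be estimated. If every site is measured for maintenance in one final window, the maintenance indicator coincides with that window's calendar effect, and the model is said to adjust for calendar time. Maintenance is named in aim 1 and linked to aim 3 in Table 2, and guidance on sustaining the programme is a stated product of the study.

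**Working it through.** **1. Timeline.** Inputs from the design section: 3 months of baseline, 6-month stagger, 6 months of active IF, then 6 months of step-down.

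- Wave w starts IF at month 3 + 6(w − 1): months 3, 9, 15.
- Active IF ends 6 months later: months 9, 15, 21.
- Adding 9 to 12 months gives months 18–21, 24–27, 30–33.
- If IF is taken to end with step-down (months 15, 21, 27), the windows are months 24–27, 30–33, 36–39.

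Successive windows start 6 months apart and each lasts 3 months, so they never overlap. One calendar window can equal at most one of them, whatever the study end.

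**2. Time since active IF ended, for a common final window.**

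| Assumed study end | Window | Wave 1 | Wave 2 | Wave 3 |
|---|---|---|---|---|
| Month 33 | 30–33 | 21–24 | 15–18 | 9–12 |
| Month 27 | 24–27 | 15–18 | 9–12 | 3–6 (still in step-down) |

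With an end at month 33, wave 1 is 12 months and wave 2 is 6 months later than the stated window.

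**3. Estimability with a common window at months 30–33.** Fixed-effects design: three wave effects, 3-month calendar quarters, and indicators for IF, step-down and maintenance (IAU as reference). The rows are all quarters to the end of each wave's step-down, plus the maintenance window.

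- Categorical time: 3 + 9 + 3 = 15 columns, rank 14. The maintenance column equals the column for the final quarter. Neither maintenance versus IAU nor maintenance versus IF is estimable; IF versus IAU is.
- Linear time: 3 + 1 + 3 = 7 columns, rank 7. The contrast is estimable, but only by projecting the trend into a window where every site is in maintenance.

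**4. Estimability with site-anchored windows (18–21, 24–27, 30–33).**

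- All quarters, categorical time: rank 15 of 15.
- All IAU quarters plus the last 3 months of IF, of step-down and of maintenance: rank 13 of 13.
- Only the last 3 months of each phase, one window per phase and site: rank 10 of 11 categorical, 6 of 7 linear.

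The last result can be seen directly. Number the phases h = 0 (IAU), 1 (IF), 2 (step-down), 3 (maintenance). The window for phase h in wave w starts at month 6(h + w − 1), so phase is an exact linear function of calendar time and wave. For the same reason the gap from the last 3 months of active IF to maintenance is 12 months in every wave (6–9 to 18–21, 12–15 to 24–27, 18–21 to 30–33), and a within-site change over that gap cannot be told from a 12-month secular trend. In this restricted set IF versus IAU is not separated from time either; that follows from which quarters are used, not from the Maintenance row.

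**The case against.** A consistent reading exists. Both operative columns give the site-relative window, the sustainment interviews fall 1 year after the facilitation phase at each site, and months 9–12 are the last quarter of that year. The phrase about the end of the study may be shorthand for each site's own last quarter, and the missing figure may show this. That reading is plausible and is the one the fix adopts. The row still does not say it, and the Reach row uses a different phrase, tied to study phases. This is a conflict between two stated definitions, not detail that an article leaves out.

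Three stronger conclusions are tempting, and the document does not support them.

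- **Maintenance is not estimable as planned.** This needs both the common-window reading and categorical calendar periods. The article states no form for calendar time, and with a linear trend the contrast is estimable by extrapolation.
- **Anchoring the window by site cures the aliasing.** It does not if only the last 3 months of each phase enter the model.
- **The absence of sites in IAU after month 15 is part of the error.** It is inherent in a design where every site crosses over. The limitations section acknowledges possible time trends and the lack of a true control group.

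Severity is also limited. Reach is the primary implementation outcome, the data are routine CDW extracts, and sustainment is also assessed by survey and interview.

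**Conclusion.** The point holds as a contradiction in the timing of a named, non-primary outcome. The two windows in the Maintenance row can agree for at most one wave of three under any study end, whether IF is taken to end with active facilitation or with step-down. If the study ends at month 33, two waves of about six sites each would be measured 6 and 12 months later than the stated window.

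The loss of estimability is conditional. It applies if the window is common to all sites, falls after wave 3 has finished step-down, and calendar time is categorical; with a parametric trend the result depends on extrapolation. The rank results assume 3-month periods and wave effects. Neither Maintenance timing enters the definition of Reach, so this contradiction does not affect the primary Reach contrast.

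**What to change.** 1. In the Maintenance row of Table 2, replace the reference to the last 3 months of the study with 9–12 months after IF ends at each site.
2. State whether IF ends with active facilitation (months 18–21, 24–27, 30–33) or with step-down (months 24–27, 30–33, 36–39), and check that Fig. 1 agrees.
3. Fit the maintenance model to all available CDW quarters, at minimum every IAU quarter together with the IF, step-down and maintenance windows, and not only the last 3 months of each phase.
4. Report any common end-of-study window descriptively, by wave, with time since IF shown.

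The cost is a table edit, more CDW quarters in the model, and CDW data to month 33 (or month 39) for wave 3. It should be settled before the extract dates are fixed.

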**Methods/design:**

This paper describes the planned evaluation of VA’s nationwide implementation of IPV screening programs in primary care clinics through a randomized implementation-effectiveness hybrid type 2 trial. With the support of our VA operational partners, we propose a stepped wedge design to compare the impact of two implementation strategies of differing intensities (toolkit + implementation as usual vs. toolkit + implementation facilitation) and investigate the clinical effectiveness of IPV screening programs. Using balanced randomization, 16–20 VA Medical Centers will be assigned to receive implementation facilitation in one of three waves, with implementation support lasting 6 months. Implementation facilitation in this effort consists of the coordinated efforts of the two types of facilitators, external and internal. Implementation facilitation is compared to dissemination of a toolkit plus implementation as usual. We propose a mixed methods approach to collect quantitative (clinical records data) and qualitative (key informant interviews) implementation outcomes, as well as quantitative (clinical records data) clinical effectiveness outcomes. We will supplement these data collection methods with provider surveys to assess discrete implementation strategies used before, during, and following implementation facilitation. The integrated-Promoting Action on Research Implementation in Health Services (i-PARIHS) framework will guide the qualitative data collection and analysis. Summative data will be analyzed using the Reach Effectiveness Adoption Implementation Maintenance (RE-AIM) framework.

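### The GEE text names only the woman as the level of correlation although VAMCs are assigned, and mixes marginal and random-effects models; if VAMC correlation is omitted, standard errors are too small

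*Protocol article*

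**What the plan says.** **Unit of assignment.** The abstract states that "16–20 VA Medical Centers will be assigned to receive implementation facilitation in one of three waves". The section on the stepped wedge trial design adds the step structure, "with about six sites assigned to each of the three waves with start times staggered by 6-month intervals", and assigns the 5-item or 1-item screener to sites within each wave. It also states that "all sites will start with the less intensive implementation strategies (toolkit + IAU) before receiving the more intensive implementation support", so each VAMC is observed under both conditions.

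**Analysis model**, all from the section on quantitative evaluation of the implementation outcomes:
- On dependence: "GEE also accommodates repeated measures (within-subject correlation), random effects (subject), moderate imbalance among independent factors (sites), and various types of missing data".
- On the model for every RE-AIM domain: "Analyses in each of these domains within the GEE framework will consist of logistic regression with random effects".
- On structure, the method is said to allow the team to "explore the study outcomes using a nested approach (WVs within VAMCs within study conditions").
- The same section adjusts for site characteristics and calendar time, and leaves correlation structures and variance components to exploration.
- It then says these analyses will be repeated to compare the two screeners.

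The section never names the VAMC as the GEE cluster or as a random effect.

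**The concern.** Three statements do not fit the design.

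1. **Level of dependence.** Women in one VAMC share staff, facilitator, toolkit uptake and screener, and the VAMC is what is assigned. Correlation within VAMC therefore has to enter the variance. The text names only the woman. That level also fits the outcomes poorly. Table 2 restricts the reach denominator to women not screened in the prior year, so repeated records on one woman cannot be the main dependence. Adoption and fidelity count clinics, for which a woman-level random effect has no meaning.

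2. **Type of model.** GEE is marginal and contains no random effects. A random-effects logistic model is conditional, and its odds ratio is a different quantity. A reader cannot tell which one the primary analysis will report.

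3. **Structure.** In a stepped wedge every VAMC crosses the conditions. Nesting VAMCs within conditions would treat one site before and after its step as two unrelated sites.

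At stake are the nominal 5% level and the interval widths for reach, the primary implementation outcome, and for the screener comparison in aim 2a, where all the information lies between sites.

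**Working it through.** **The plan's own figure.** The section on power analyses states power above 90% at 5% type I error. It gives no rates, effect size, number of women, ICC or sidedness, so the figure cannot be reproduced.

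**Inputs from the article.** "We aim to recruit 16–20 VA Medical Centers (VAMCs) as sites", in three waves of about six; "All sites will start with 3 months in the less-intensive toolkit + IAU condition".

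**Assumptions, none from the article.** 18 sites, six per wave; four calendar periods (baseline and three steps); m = 30–300 women per site-period; ICC 0.01–0.10; cluster autocorrelation (CAC) 1.0 or 0.8; linear approximation on site-period means with total variance 1. Results for 16 and 20 sites are nearly identical.

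**True variance.** Each site-period mean has its own variance ICC(1 − CAC) + (1 − ICC)/m, plus ICC × CAC shared by all periods of the same site. Let k be the true SE divided by the reported SE. Actual type I error is then 2Φ(−1.96/k).

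**(a) No site term.** The reported variance of a site-period mean is 1/m. With period means removed, the condition indicator is zero in periods 1 and 4.
- Period 2: +2/3 for wave 1, −1/3 for waves 2 and 3.
- Period 3: +1/3 for waves 1 and 2, −2/3 for wave 3.
- Sum of squares over cells: 4 + 4 = 8.
- Site totals are +1, 0 and −1 by wave; their sum of squares is 6 × (1 + 0 + 1) = 12.
- The shared site component is therefore multiplied by 12/8 = 1.5.

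Hence k² = (1 − ICC) + m·ICC·[(1 − CAC) + 1.5·CAC].

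| m | ICC | k² (CAC 1) | k; type I | k² (CAC 0.8) | k; type I |
|---|---|---|---|---|---|
| 30 | 0.01 | 0.99 + 0.3 × 1.5 = 1.44 | 1.20; 10% | 0.99 + 0.3 × 1.4 = 1.41 | 1.19; 10% |
| 100 | 0.05 | 0.95 + 5 × 1.5 = 8.45 | 2.91; 50% | 0.95 + 5 × 1.4 = 7.95 | 2.82; 49% |
| 300 | 0.10 | 0.90 + 30 × 1.5 = 45.9 | 6.77; 77% | 0.90 + 30 × 1.4 = 42.9 | 6.55; 76–77% |

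**(b) Site fixed effects, women otherwise independent.** The shared site component drops out:

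k² = [ICC(1 − CAC) + (1 − ICC)/m] ÷ {[(1 − ICC) + ICC(1 − CAC)]/m}.

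- CAC 1: k = 1, type I error 5%.
- CAC 0.8, m 30, ICC 0.01: 0.0350/0.0331 = 1.06; k = 1.03; 5.7%.
- CAC 0.8, m 100, ICC 0.05: 0.0195/0.0096 = 2.03; k = 1.43; 17%.
- CAC 0.8, m 300, ICC 0.10: 0.0230/0.00307 = 7.5; k = 2.74; 47%.

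**(c) VAMC nested within condition.** Model-based SEs assume that a site's two conditions are uncorrelated. Over the same grid, k runs from 0.95 down to 0.23 (CAC 1) or from 0.96 down to 0.59 (CAC 0.8). Type I error is at or below about 4%, so reported SEs are too large.

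**(d) Screener comparison (aim 2a).** The screener varies only between sites, so site fixed effects cannot be used. Within one period, ignoring site understates the SE by √(1 + (m − 1)·ICC). With m = 100 and ICC 0.05 this is √(1 + 99 × 0.05) = √5.95 = 2.44, and the type I error is 2Φ(−1.96/2.44), about 42%.

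**(e) VAMC as the cluster.** Simulation without a treatment effect (4,000 runs; m = 100, ICC 0.05, CAC 0.8), type I error for 16/18/20 sites:
- uncorrected sandwich, normal reference: 10.3%/9.3%/8.5%
- uncorrected sandwich, t with (sites − 2) df: 7.6%/7.1%/7.0%
- leverage-corrected sandwich, same t: 4.5%/4.2%/4.5%

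**The case against.** The strongest defence is that the sentence on within-subject correlation lists what GEE can handle and does not specify the final model. The sentence that does commit to a model gives no level for its random effects. VAMC clustering is therefore not excluded, and the section does refer to between-site and within-site effects, counts per site and women within VAMCs. In that setting, independent factors most naturally means predictors and does not assert that sites are statistically independent. This stands, and it makes the consequence conditional. It does not remove the defect: the one level that is named is wrong for this design, and the committed model combines two incompatible types.

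A reader might infer more than the article supports:
- **That all three features make SEs too small.** Only omission of VAMC correlation does. The nesting works the other way and is offered for exploration only. Mixing marginal and conditional models blurs the estimand but has no fixed direction of SE error.
- **That ten site covariates will exhaust the cluster-level degrees of freedom.** The Table 1 variables feed the balancing algorithm. The article does not say that all of them enter the outcome model.
- **That an uncorrected sandwich with a normal reference is planned.** No variance estimator is stated, and that detail may properly sit in the SAP. Its absence is no fault here; the results in (e) only inform the remedy.
- **That the power claim is false.** It cannot be checked. Clustering may have been allowed for.

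**Conclusion.** The point holds in conditional form. The article misstates the analysis model: it names the woman as the only level of correlation while VAMCs are assigned, places random effects inside GEE, and describes as nested a structure that is crossed. An SAP could add detail, but these statements would still need correcting.

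If the woman-level description is followed and VAMC correlation is left out, the true SE for reach is about 1.2 to 6.8 times the reported one, with type I error of about 10% to 77%. Site fixed effects remove the problem for the within-site contrast only if within-site correlation is constant over time; at CAC 0.8 the error rate is 5.7% to 47%. They offer no help for the screener comparison, where the SE is understated about 2.4-fold at m = 100 and ICC 0.05.

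The direction is secure given the omission. The size rests entirely on assumed ICC, CAC and cluster sizes and on the simplified four-period layout.

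**What to change.** State one primary model. One suitable choice is a logistic GEE with VAMC as the cluster, calendar-period effects, condition (crossed with VAMC) and assigned screener, using a bias-corrected sandwich variance and a t reference suited to 16–20 clusters. In the simulation above, this kind of inference brought type I error to 4.2–4.5%. The alternative is a logistic mixed model with random VAMC and VAMC-by-period effects, reported as a conditional odds ratio.

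If GEE is kept, delete the references to random effects. In either case delete the nesting of VAMCs within study conditions. For the clinic-level adoption and fidelity outcomes, state that clinics are the observations and VAMC the cluster.

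The cost is a few sentences of protocol and SAP text and options in standard software. Intervals will be somewhat wider than those from an analysis that ignores site.
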